### Strategies to improve adherence to interventions {11c}

As the interventions of the TRIANGLE trial (experimental and control groups) are surgical interventions, strategies to improve adherence to the allocated intervention are not needed.

### Relevant concomitant care permitted or prohibited during the trial {11d}

Additional perioperative care of the patients will be performed according to the institutional standards. All additional medications and/or treatments are permitted during the trial when considered necessary by the treating physician.

### Provisions for post-trial care {30}

The post-trial care of the patients will be the regular tumour follow-up according to the current guidelines. No compensation will be provided.

### Outcomes {12}

#### Primary endpoint

The primary endpoint of the TRIANGLE trial will be the DFS after resection, defined “as the time from randomisation until disease recurrence or death from any cause” [22]. Disease recurrence can be a local recurrence or distant metastases. Given the overall dismal prognosis of PDAC, the high rate of recurrence as well as the objective of the trial, i.e. to reduce recurrence rates and improve OS, DFS seems the logical and most relevant endpoint for the TRIANGLE trial. It is a frequent endpoint in cancer trials in the adjuvant setting after definitive surgery, and it is widely accepted by regulatory authorities worldwide [22, 23] and has been used in previous randomised controlled trials (RCTs), thus allowing the comparison of data between trials [16, 24, 25]. Furthermore, it is based on objective and quantitative assessments. DFS is patient-relevant as it includes all-cause mortality and recurrence. In order to avoid detection bias, follow-up will be standardised for both groups and include clinical outpatient visits, contrast-enhanced CT scan and tumour markers every 6 months for 3 years.

#### Primary estimand

In the recently released addendum to the ICH E9 guideline (final version), the estimand framework is recommended as clear and transparent definition of “what needs to be estimated to address a specific scientific question of interest”. Such an estimand should be defined through the treatment condition of interest, the population of interest, variable of interest, specification of how intercurrent events are handled, and summary measure. The specification of how intercurrent events are handled is referred to as intervention effect in the following. This way a more precise definition of the treatment effect of interest in relation to the trial objective(s) is enabled. Based on such an estimand, adequate methods to estimate this estimand can be chosen. In the following, the primary estimand (see Table 1) corresponding to the primary objective is described.

**Table 1 Tab1:** Overview of the primary estimand

**Analysis**	**Treatment**	**Population**	**Variable**	**Intervention effect (strategy)**	**Summary measure**
Primary	Specified in Intervention description (11a)	Defined by the in- and exclusion criteria	DFS	Death: composite Incomplete observation due to loss to follow-up or early drop-out: hypothetical Others: treatment policy	Hazard ratio (Cox proportional hazards regression model)

Treatment: The treatments patients will receive in the experimental group or in the control group of the trial are specified as mentioned above.

Population: The targeted population is defined through the in- and exclusion criteria.

Variable: The variable is disease-free survival after resection, defined as the time from randomisation until disease recurrence (local recurrence or distant metastases) or death from any cause.

Intervention effect: Possible intercurrent events and the strategies to handle them are as follows: Death, as an intercurrent event occurring after randomisation, is handled by inclusion into the definition of the primary endpoint which reflects a composite strategy. Patients with incomplete observation time due to loss to follow-up or early drop-out will be censored at the last observation, which reflects a hypothetical strategy. Besides these events, other post-randomisation events (e.g. intervention not as randomised, discontinuation of chemotherapy) will not be considered, thus reflecting a treatment policy approach, which means that the effect of randomised treatment is estimated irrespectively of other post-randomisation events not captured in the primary endpoint definition. This corresponds to the intention-to-treat (ITT) principle.

Summary measure: The summary measure is the adjusted hazard ratio.

#### Secondary endpoints

Secondary endpoints of the TRIANGLE trial are as follows:Rate of the following:Microscopically complete margin clearance (> 0.1 cm margin clearance, R0(CRM-))Microscopic margin clearance ≤ 0.1 cm (R0(CRM+))Microscopic margin involvement (R1) resections according to the 8th edition of the UICC TNM classificationRate of the following PD-associated postoperative complications within 90 days after the index operation:Postoperative pancreatic fistula (POPF) as defined by the International Study Group of Pancreatic Surgery (ISGPS) [26]Postpancreatectomy haemorrhage (PPH) as defined by the ISGPS [27]Delayed gastric emptying (DGE) as defined by the ISGPS [28]Bile leakage as defined by the International Study Group of Liver Surgery (ISGLS) [29]Lymphatic fistula as defined by the ISGPS [30]Diarrhoea as graded by the Common Terminology Criteria for Adverse Events (CTCAE) version 5.0 [31]All other postoperative complications graded according to the Dindo-Clavien classification [32] within 90 days. This endpoint complements the PD-associated complications evaluated via the above-mentioned ISGPS endpoints, to assess all remaining postoperative complications to establish a risk-benefit assessment of the two interventions.Overall survival within the study period.Local recurrence within the study period.Quality of life (QoL) according to the European Organisation for Research and Treatment of Cancer (EORTC) QLQ-C30 and PAN26 at discharge and during every follow-up visit compared to baseline.Quality of recovery (QoR) according to the QoR-15 questionnaire on postoperative day 5 compared to baseline.Length of primary hospital stay in days from the day of index operation to the day of discharge.Serious adverse events (SAEs) in both groups .

### Participant timeline {13}

Patients scheduled for elective PD will be screened preoperatively (visit 1). After the patient has given informed consent, the inclusion and exclusion criteria are assessed during the screening visit. Patients fulfilling all the inclusion criteria and none of the exclusion criteria and who consent to take part in the trial are randomised during surgery (visit 2; surgery and randomisation) after the surgeon has obtained certainty that both interventions can be performed in the patient. The results of the pathologic work-up (secondary endpoint) will also be recorded in the eCRF section of visit 2. Patients are planned for follow-up visits on postoperative days 5, 10–12 and 90 (visits 3, 4 and 6) for the evaluation of primary and secondary endpoints. Visit 5 will be performed at discharge. If discharge occurs before visit 3 or 4, the respective postoperative visits (3 or 4) can be omitted. In addition, 6, 12, 18, 24, 30 and 36 months (visits 7–12) after surgery, patients are planned for follow-up visits to evaluate primary and secondary outcome parameters (Fig. 1 and Table 2).

**Fig. 1 Fig1:**
[figure not shown]
Flow chart of the TRIANGLE trial. F/U, follow-up; POD, postoperative day; PD, partial pancreaticoduodenectomy; R, randomisation. *Respective visits are skipped if the patient has been discharged before

**Table 2 Tab2:** Trial visits and documented parameters

**Visit**	**1**	**2**	**3–4**^a^	**5**	**6**	**7–12**
**Time point**	Screening	Day of surgery, pathology	POD 5 POD 10–12	Day of discharge	POD 90	POM 6, 12, 18, 24, 30, 36 (or pre-mature trial termination)
**Type of visit**	Inpatient	Inpatient	Inpatient	Inpatient	Outpatient (inpatient) (telephone)	Outpatient (telephone)
Written informed consent	**X**					
Preoperative inclusion/exclusion criteria	**X**					
Intraoperative inclusion criteria		**X**				
Demographics and baseline data	**X**					
Medical history	**X**					
Surgery data		**X**				
Randomisation		**X**				
*Primary endpoint*						
Disease-free survival			**X**	**X**	**X**	**X**
*Secondary endpoints*						
Pathologic data		**X**				
Postoperative morbidity			**X**	**X**	**X**	
Length of hospital stay				**X**		
Overall survival			**X**	**X**	**X**	**X**
Local recurrence			**X**	**X**	**X**	**X**
*Patient-reported outcomes (PRO)*						
Quality of recovery^c^	**X**		**(X)**^d^			
Quality of life assessment^b^	**X**			**X**		**X**
*Safety*						
SAE		**X**	**X**	**X**	**X**	**X**

*POD* Postoperative day, *POM* Postoperative month, *PRO* Patient-reported outcome, *SAE* Serious adverse events

^a^Skip respective visits if the patient has been discharged prior to visit

^b^According to EORTC QLQ-C30 and -PAN26

^c^According to the QoR-15

^d^Only on POD 5

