#### Data management {19}

An eCRF will be used for data collection. The study data will be collected using REDCap [37] (Research Electronic Data Capture), a secure, web-based data capture application hosted at the IMBI. To assure a safe and secure environment for the data acquired, data transmission is encrypted with secure socket layer (SSL) technology. The database server is located in a secure data centre and is protected by a firewall. The system provides an infrastructure to support user roles and rights. Only authorised users are able to enter or edit data; the access is restricted to data of the patients in the respective centre. All changes to data are logged with a computerised timestamp in an audit trial. All clinical data will be pseudonymised. Backups are conducted regularly.

All protocol-required information collected during the trial must be entered by the investigator or designated representative in the eCRF. For health-related quality of life and patient-reported outcome data, patients may directly enter the data in the eCRF. Alternatively, paper-based reported outcome questionnaires must be entered by the investigator or designated representative in the eCRF. The investigator or designated representative should complete the eCRF forms as soon as possible after information is collected, preferably on the same day that a trial subject is seen for an examination, treatment, or any other trial procedure. Any outstanding entries must be completed immediately after the final examination. An explanation should be given for all missing data. The completed eCRF must be reviewed and signed by the local investigator or by a designated sub-investigator.

To guarantee high data quality, data validation rules will be defined in a data validation plan. Completeness, validity and plausibility of data will be checked at the time of data entry (edit checks) and using validating programs, which will generate queries. The investigator or the designated representatives are obliged to clarify or explain the edit checks and queries. If no further corrections are to be made in the database, eCRF data will be locked.

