## Statistical methods

### Statistical methods for primary and secondary outcomes {20a}

The primary outcome disease-free survival is compared between the groups using a Cox proportional hazards model adjusted for the covariates treatment group, age, neoadjuvant treatment, adjuvant treatment as fixed effects and centre as a random effect. It can be expected that applying the Cox proportional hazards model will lead to an increase in power in comparison with a log-rank test. Confounding by other less important prognostic and predictive factors can be assumed to be controlled by the randomised trial design. The significance level is set to 5% (two-sided). The confirmatory analysis is conducted based on the full analysis set (FAS) according to the ITT principle, i.e. all randomised patients are included and analysed in the treatment group as randomised which reflects a treatment policy approach (according to the ICH E9 (R1) addendum). Death, as an intercurrent event occurring after randomisation, is handled by inclusion into the definition of the primary endpoint which reflects a composite strategy.

All secondary outcomes will be evaluated descriptively, and descriptive *p*-values for the corresponding effects will be reported along with 95% confidence intervals. Continuous variables will be described using a number of missing values, non-missing values, mean, standard deviation, median, Q1, Q3, minimum and maximum. For binary or categorical variables, absolute and relative frequencies will be provided. Thereby, binary and categorical variables will be compared by the chi-squared tests, and continuous variables will be compared with *t*-tests. OS will be analysed analogously to the primary endpoint with a Cox proportional hazards model. QoL will be analysed using linear mixed models with baseline score, age, treatment group and the stratification variables as covariates; centre and time point will be included as random effects. Furthermore, the treatment effect for secondary endpoints will be assessed descriptively within several subgroups to identify potential prognostic and predictive factors. Analyses of secondary endpoints will be based on the ITT population. No imputation of missing values will be conducted in the analyses of secondary endpoints.

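### Day-5 QoR-15 is skipped in patients already discharged, so its values go missing selectively from the fastest recoverers

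*Protocol article*

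**What the plan says.** The protocol article lists this secondary endpoint: "Quality of recovery (QoR) according to the QoR-15 questionnaire on postoperative day 5 compared to baseline". In Table 2 the instrument is marked at screening and once after surgery, in the column for visits 3 and 4, with a footnote restricting it to day 5. Visit 3 is therefore its only postoperative slot, and that column is typed as inpatient.

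Three places deal with patients who have already left hospital. Table 2, footnote a, is an instruction: "Skip respective visits if the patient has been discharged prior to visit". The Fig. 1 legend likewise says that the visits are skipped. The Participant timeline section is permissive: "If discharge occurs before visit 3 or 4, the respective postoperative visits (3 or 4) can be omitted".

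On analysis, the Statistical methods section compares continuous secondary outcomes by t-test and adds: "No imputation of missing values will be conducted in the analyses of secondary endpoints".

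Remote collection exists elsewhere in the plan. The section on retention and follow-up {18b} allows telephone visits after discharge. The Data management section says of patient-reported data that "patients may directly enter the data in the eCRF".

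The cancer-specific quality-of-life endpoint is defined as "QLQ-C30 and PAN26 at discharge and during every follow-up visit compared to baseline". Its first postoperative sample belongs to visit 5: "Visit 5 will be performed at discharge". The same endpoint list contains "Length of primary hospital stay in days from the day of index operation to the day of discharge".

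**The concern.** The QoR-15 endpoint is defined for a fixed day in all patients, but the schedule observes it only in those still in hospital on that day. Being in hospital on day 5 is a consequence of recovery, which is what the questionnaire measures. The missing values would therefore tend to be the good ones. A t-test on the observed values compares two groups that have each lost part of their upper tail. If one arm sends more patients home early, it loses more of its best scores and looks worse than it is.

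There is a plausible route to such a difference. The retrospective comparison cited in the Discussion reports diarrhoea in 34.4% after the TRIANGLE operation and 14.4% after conventional surgery. If that slows discharge, the control arm would lose more of its high QoR-15 scores and early harm would be understated.

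The loss occurs at collection, so a later analysis plan cannot recover the values. The mix of a directive and a permissive rule also lets sites act differently.

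A related and lesser matter is the discharge sample of QLQ-C30/PAN26. Its postoperative day is set by length of stay, itself a secondary endpoint, so the two arms may be sampled at different times after surgery.

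**Working it through.** The plan states no figure on this point, so there is nothing to reproduce. The first step is a reading of the schedule; the rest shows how large the effect could be.

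**1. Who has a value?**
- Still in hospital on day 5: visit 3 takes place and QoR-15 is collected.
- Home before day 5: visit 3 is skipped (footnote a, Fig. 1 legend) or may be omitted (Participant timeline). No other postoperative QoR-15 is scheduled and nothing is imputed, so the patient drops out of the comparison.

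**2. Size for QoR-15, selection model**

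From the documents: 135 patients per arm (Sample size section). Assumed, because the documents give nothing: the share *f* of an arm home before day 5 (0 to 20%), and the correlation ρ between speed of recovery and the QoR-15 score (0.3 to 0.7). There is no true treatment effect.

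If the best-recovering fraction *f* is unobserved and scores are standard normal, the observed mean falls by ρ·L(f), where L(f) = φ(c)/(1 − f) and c = Φ⁻¹(1 − f):
- f = 2%: 0.0484/0.98 = 0.049
- f = 5%: 0.1031/0.95 = 0.109
- f = 10%: 0.1755/0.90 = 0.195
- f = 20%: 0.2800/0.80 = 0.350

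The spurious arm difference is ρ·[L(f₁) − L(f₂)]:

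| Home before day 5, one arm vs the other | Difference in SD, ρ = 0.3 to 0.7 |
|---|---|
| equal shares | 0 |
| 5% vs 2% | 0.02 to 0.04 |
| 10% vs 5% | 0.03 to 0.06 |
| 10% vs 2% | 0.04 to 0.10 |
| 20% vs 10% | 0.05 to 0.11 |

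A cruder model agrees. If the early leavers score 1 SD above the rest, the observed mean falls by f × 1 SD, and 10% vs 2% gives 0.10 − 0.02 = 0.08 SD.

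**3. Yardstick**

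The standard error of a mean difference is √(2/135) = 0.122 SD. The difference detectable with 80% power at two-sided 5% is (1.960 + 0.842) × 0.122 = 0.34 SD. With no true effect, a spurious 0.02 SD raises the nominal 5% rejection rate to 5.3%, 0.05 SD to 7.0% and 0.10 SD to 13%.

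**4. Discharge QLQ-C30/PAN26**

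Assume that scores recover by 0.02 to 0.05 SD per day and that mean stay differs by *d* days. The shift in the discharge contrast, read as quality of life at equal time since surgery, is slope × *d*:
- d = 0: 0
- d = 2: 0.04 to 0.10 SD
- d = 5: 0.10 to 0.25 SD

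The documents give no length of stay and no recovery slope, so these are scenarios only. They concern the discharge time point alone, not the planned mixed model over all visits.

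**The case against.** The strongest reply has four parts.

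*The bias is conditional.* It is zero when early-discharge rates are equal, and the documents show no difference. The Discussion reports comparable perioperative morbidity apart from diarrhoea, and a similar picture in the preceding single-centre trial's interim safety data. This stands. A reader might infer from the schedule that the arms are not compared like with like; the documents support only that they might not be.

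*Few patients are affected.* The schedule places inpatient visits at day 5 and again at days 10 to 12, which suggests that few are expected home before day 5. This stands too, and it is why the effect is probably small.

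*The text already permits remote collection.* The Participant timeline only allows omission, and telephone contact and self-entry are foreseen. This stands in part. Footnote a and the Fig. 1 legend say to skip, and a site following Table 2 would not collect the value.

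*Quality of life at discharge is a chosen endpoint.* The endpoint list and Table 2 agree on it, and it answers a sensible question beside length of stay. A reader might infer that it hides harm in the arm that stays longer and must move to a fixed day. The documents do not support that: no difference in stay is shown, and the six assessments at months 6 to 36 have fixed times. With equal weights over seven postoperative samples, even the extreme 0.25 SD would shift an averaged effect by 0.25/7, about 0.04 SD. A fixed sample at days 10 to 12 would also bring its own selection, because the sickest patients are least able to answer.

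**Conclusion.** The point holds for QoR-15. The endpoint is promised on day 5, but its only postoperative assessment is dropped for patients already home, and nothing replaces the missing values. Missingness then depends on a post-randomisation outcome and falls on the fastest recoverers.

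Bias in the comparison needs unequal early-discharge rates, which the documents neither report nor exclude. Its size is probably small, about 0.02 to 0.1 SD. That range rests wholly on assumed discharge shares and an assumed link between recovery and score. Only a descriptive secondary endpoint is affected; disease-free survival, the 90-day complications, graded diarrhoea and serious adverse events do not depend on it. The case for acting is that the remedy costs almost nothing and the data cannot be recovered later.

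For the discharge QLQ-C30/PAN26 sample, the conclusion concerns interpretation. It describes state at discharge, not quality of life at equal time since surgery. The larger shifts computed for it do not establish that the planned endpoint is wrong.

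**What to change.** 1. Amend footnote a, the Fig. 1 legend and the Participant timeline text to one consistent rule: visits 3 and 4 may be dropped after discharge, except that QoR-15 is obtained on day 5 from every patient. Those already home answer by telephone or enter it themselves in the eCRF, both already provided for.
2. Record the date and route of completion, and report by arm how many patients were home before day 5 and how many QoR-15 values are missing.
3. Keep the discharge QLQ-C30/PAN26 sample. Report the actual postoperative day by arm beside it and describe the between-arm contrast as state at discharge. Adding or substituting a fixed-day early sample is optional, given the selection it would bring.

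The cost is a wording amendment and a few reminders or calls; no new instrument or visit is needed. Some answers will come by a different route, which is why the route should be recorded. The change does not recover values from patients too ill to answer on day 5, or from any who passed that day before the amendment.

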### Sample size {14}

The sample size calculation is based on the primary endpoint disease-free survival. The assumptions are based on a median survival time of 14 months in the control group and 21 months in the treatment group resulting in a corresponding hazard ratio of 0.667 assuming exponentially distributed survival times [7, 16, 33]. To detect the assumed difference using a log-rank test at a significance level of 5% (two-sided) with a power of 80%, a total number of 192 events (i.e. recurrence or deaths) are required for the entire trial. It is expected that applying the Cox proportional hazards model, as described below, will lead to an increase in power. With an accrual period of 30 months and a follow-up period of at least 36 months, and assuming an exponentially distributed drop-out rate of 20% (at 66 months), *n* = 270 (135 per group) patients are needed (based on the approximation formula by Schoenfeld). The sample size calculation was done using ADDPLAN 6.1.1.

### Recruitment {15}

In order to recruit the necessary number of patients, at least seven pancreatic cancer centres will participate in this trial. All participating trial sites will be high-volume centres with broad expertise in pancreatic surgery and have the necessary expertise, equipment and personnel to perform this trial. Most of the centres are part of the CHIR-Net.

